#### Participant recruitment

2.4.5

We aim to recruit about 20 parents (320 total), 20 students (320 total), and 10 HSRC implementers (160 total) at each school (two cohorts of *n* = 8 schools) enrolled in the study. We will share recruiting materials online (e.g., email) and in-person (e.g., back-to-school events, student drop-off and pickup) to provide details about the study. Parents agreeing to participate will complete the consent form for their child and themselves, a short survey at pre- and post-intervention, and they will be compensated with a $10 gift card at each time point. The research team will meet in-person with children who have received signed parental consent to explain the study and answer any questions. Children will sign an assent form before participating in a survey and biometrics assessment at pre- and post-intervention. They will also receive an item worth $10–$15 (e.g., t-shirt, water bottle, active toy) for each data collection timepoint (pre- and post-intervention). Children who do not agree to participate in the study will still be allowed to participate in HSRC programs. HSRC implementers (e.g., Extension agents, school staff, administrators) will complete a consent form agreeing to participate, a survey pre- and post-intervention, and interviews following the intervention. They will be compensated with a $20 gift card for each survey and $50 for the interview.

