#### Randomization

2.4.6

In each of the two cohorts, schools will be randomized to one of eight experimental conditions and will receive a different combination of implementation strategies (Table 2). In each school year, four schools will receive each implementation strategy, and four schools will not (all schools will receive the website as a constant implementation strategy). Schools and data collectors will be blinded to randomized conditions until a school completes data collection. An interim analysis (following processes outlined below) will be conducted between the two cohorts to determine if implementation strategies should be removed and/or replaced, as well as if any of the current implementation strategies should be modified.

**Table 2 tab2:** Randomized experimental conditions for this study.

Experimental condition	Constant	Factor 1	Factor 2	Factor 3
1	Website/TEKS alignment	None	None	None
2	Website/TEKS alignment	None	None	Enhanced engagement opportunities
3	Website/TEKS alignment	None	School-to-school mentoring	None
4	Website/TEKS alignment	None	School-to-school mentoring	Enhanced engagement opportunities
5	Website/TEKS alignment	Additional resources	None	None
6	Website/TEKS alignment	Additional resources	None	Enhanced engagement opportunities
7	Website/TEKS alignment	Additional resources	School-to-school mentoring	None
8	Website/TEKS alignment	Additional resources	School-to-school mentoring	Enhanced engagement opportunities

Each of the 8 conditions will be randomized one time per cohort.

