#### Other implementation outcomes

2.5.2

To measure other variables in our logic model, the implementer survey will ask about the acceptability, appropriateness, and feasibility of implementing the HSRC initiative (39). We will also assess school characteristics related to the implementation of the HSRC initiative (e.g., school culture, leadership engagement, resources) using an existing measure of the inner setting from the Consolidated Framework for Implementation Research (40). Existing validated measures will also be modified to evaluate implementers’ perceptions of the HSRC initiative (e.g., knowledge, attitudes, and self-efficacy) (41). To determine if HSRC programming had any effect on implementer health behaviors, implementers (e.g., principals, teachers, extension agents, and support staff involved with HSRC’s delivery) will be asked about their physical activity and eating behaviors (42, 43).

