#### Statistical and power analysis

2.6.1

This is an optimization study to screen and refine components of a support strategy for the HSRC initiative in preparation for a fully powered randomized controlled trial; thus, this study is not fully powered to examine differences in implementation or effectiveness outcomes (60). To analyze outcomes, we will use univariate and bivariate statistics to determine the distribution of outcome measures and to identify relevant covariates (61). To test between-implementation strategy differences on implementation and effectiveness outcomes, students at schools with and without each implementation strategy (independent variable) will be evaluated using a generalized linear model framework. Baseline scores will be added as a covariate (when applicable), post-intervention score is the outcome, and school is a clustering variable (62). Other covariates (e.g., school size), identified in the preliminary bivariate analyses, will also be included in the model. If missing data occurs, we will mitigate potential biases by analyzing multiple imputed datasets under an intention-to-treat approach (63). Analyses will be compared to per-protocol analyses (64). Interaction effects between strategies are normally small in behavioral trials; however, we will review plots of combinations of strategies to determine if a specific combination of strategies warrants further evaluation. If so, we will add an interaction term to our model. We will calculate standardized effect estimates for each strategy (i.e., Cohen’s *d*), compare effect estimates to make decisions about which components to include in the final support strategy, and report these estimates in our results.

As the goal of this project is to refine and optimize implementation strategies for testing in a future trial, we will conduct an interim analysis following the first cohort of schools using the approach outlined above. This analysis will be repeated following the second cohort of schools. Depending on the results of the interim analysis and potential changes to the strategies that result from the interim analysis, we will conduct a pooled analysis across both cohorts, unless the implementation strategies undergo substantive modifications between cohorts, in which case we will only report the individual results from each cohort.

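### Adding covariates by uncapped bivariate screening can use up the four school-level degrees of freedom in each 8-school cohort; how much precision is lost depends on inputs the protocol does not fix

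*Protocol article*

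**What the plan says.** Section 2.6.1 (Statistical and power analysis) sets out a two-step rule. First, "we will use univariate and bivariate statistics to determine the distribution of outcome measures and to identify relevant covariates". Second, "Other covariates (e.g., school size), identified in the preliminary bivariate analyses, will also be included in the model". These terms come on top of the baseline adjustment: "Baseline scores will be added as a covariate (when applicable), post-intervention score is the outcome". In the same model "school is a clustering variable", so strategy effects are judged between schools.

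The number of schools is fixed in section 2.4.6 (Randomization). The note to Table 2 says "Each of the 8 conditions will be randomized one time per cohort", and the text says "In each school year, four schools will receive each implementation strategy, and four schools will not". Section 2.4.5 gives the numbers within schools: "We aim to recruit about 20 parents (320 total), 20 students (320 total), and 10 HSRC implementers (160 total) at each school".

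The same approach is used at the interim analysis on the first 8 schools and again after the second cohort. If the strategies change substantively between cohorts, only the separate cohort results are reported. An interaction term may be added after plots have been reviewed. Effect estimates are then compared to decide which strategies to keep.

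**The concern.** This is a stated method and not a detail left open. A statistical analysis plan that followed the article would keep the screening step, and one that fixed the covariates would depart from the published method.

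The randomised unit is the school, and there are only 8 per cohort. Student-level covariates cost almost nothing at that level, but the example given, school size, is school-level. Section 2.5.2 also measures "school characteristics related to the implementation of the HSRC initiative (e.g., school culture, leadership engagement, resources"). These are survey outcomes and are not named as covariates, but they would be school-level candidates if averaged by school.

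With so few schools, a handful of chance selections could widen the intervals for the strategy effects badly or leave nothing to estimate error with. At stake is the decision the trial exists to make: strategies are kept, changed or dropped by comparing these estimates, at the interim on 8 schools alone, and possibly in the final report on 8 schools per cohort.

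**Working it through.** **Plan's own figures.** 20 students × 16 schools = 320, and 10 implementers × 16 = 160. Both agree with section 2.4.5. No power, ICC or alpha figure is stated, so there is nothing further to reproduce.

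**Step 1: degrees of freedom (from the documents alone).** Residual school-level df = schools − intercept − 3 strategy effects − cohort term (if pooled) − interactions − school-level covariates.

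| School-level covariates | 0 | 1 | 2 | 3 | 4 | 5 |
|---|---|---|---|---|---|---|
| 8 schools, main effects | 4 | 3 | 2 | 1 | 0 | not estimable |
| 8 schools, one interaction | 3 | 2 | 1 | 0 | not estimable | not estimable |
| 16 schools pooled, with cohort term | 11 | 10 | 9 | 8 | 7 | 6 |

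**Step 2: cost per covariate.** The 95% half-width for a strategy effect is t(0.975, df) × 2 × √(VIF/n), in SDs of school means, where n is the number of schools and VIF is the variance inflation from the added covariates. With 8 schools and no covariate: 2.776 × 2 × √(1/8) = 1.96. For uninformative, normally distributed covariates (assumed), the median VIF with 1, 2 and 3 of them is 1.14, 1.58 and 2.63, and t is 3.182, 4.303 and 12.706. The median half-widths are 2.40, 3.82 and 14.57. With 16 schools the half-width goes from 1.10 with none to 1.43 with four.

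**Step 3: how often a null covariate is selected.** Assume 20 students per school, screened as independent records at p<0.05. All students in a school share the covariate, so the variance of the screening statistic is inflated by about 1 + 19 × ICC. The approximate pass rate is the two-sided normal tail beyond 1.96/√(1 + 19 × ICC):

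- ICC 0.05: 1.96/√1.95 = 1.40, about 16%
- ICC 0.10: 1.96/√2.9 = 1.15, about 25%
- ICC 0.5: 1.96/√10.5 = 0.60, about 55%

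Simulation gives about 17%, 25% and 58%. If school means are screened instead, the rate is the nominal 5%.

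**Step 4: effect on the 8-school analysis.** The simulation uses null school-level candidates, the student-level screen above, a regression of school means on the strategies with t-based inference, and no baseline covariate. Half-widths are in student-level SDs.

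| ICC (assumed) | Candidates (assumed) | Median half-width, no screening | Median half-width, screened |
|---|---|---|---|
| 0.05 | 6 | 0.56 | 0.58 |
| 0.10 | 6 | 0.69 | 0.79 |
| 0.5 | 3 | 1.31 | 1.95 |

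With 6 candidates at ICC 0.5, about half of the models have no residual df at all. With 16 schools pooled and 6 candidates, the median half-width goes from 0.78 to 0.88 at ICC 0.5, and there is no loss at ICC 0.10.

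**Step 5: dependence on the screening unit.** With 8 schools screened on school means, 10 null candidates at p<0.05 leave 0 df in 0.1% of runs. At p<0.20 they leave 0 df in 9.1% and a non-estimable model in 3.2%. Four candidates at p<0.20 leave 0 df in 0.2%. Type I error, where it could be tested, was 4.6-5.2%.

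**The case against.** The strongest reply is that most of what drives the harm is not in the document. The article gives no threshold, candidate list, screening unit or ICC. It names one covariate, and with three or fewer school-level candidates and main effects only, zero df cannot occur. Screening on school means removes the problem at p<0.05. For weakly clustered outcomes the typical interval hardly moves, and the larger SDs seen there in simulation come from a few near-saturated fits that an analyst would notice. All of this stands, and it limits the size of the point.

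Treating every candidate as null also shows only the downside. With one candidate that explains 50% of the between-school variance at ICC 0.5, the same screen lowers the SD of a strategy effect from 0.51 to 0.45 with 8 schools and from 0.36 to 0.28 with 16. At 30% it is neutral with 8 schools. This stands too, and it is why the fix keeps room for one school-level covariate.

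The remark that the study is not fully powered does not dispose of the point. It excuses wide intervals that come from the design. It does not excuse avoidable further loss when decisions rest on comparing the estimates.

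Three stronger readings go beyond the documents. A reader might infer inflated false positives, but with valid school-level df the error rate stayed near 5%. A reader might infer that dose, being derived through teachers, has a very high school-level ICC. Section 2.5.1 supports sharing within classes, and the Discussion says smaller groups within a school receive additional programmes, so 0.5 is only an assumption. A reader might also infer a different covariate set for each outcome, chosen against post-test data; section 2.6.1 says neither.

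**Conclusion.** The point holds in a conditional form. What is certain from the documents is the rule (screen, then include, with no cap, and with a school-level example) and the arithmetic: 4 school-level df per cohort, none left after four school-level covariates, and no estimate after five. One interaction brings each limit forward by one.

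The size of the loss is not certain. Under student-level screening it is small for low-ICC outcomes with few candidates, and large for strongly clustered outcomes or many candidates. It is small in the pooled 16-school analysis, although that analysis is itself conditional, and absent if school means are screened at p<0.05. These statements rest on assumed ICCs, candidate numbers and thresholds, and on candidates with no true effect. It would be wrong to conclude that the trial's strategy effects will be non-estimable. The documents show that the rule permits this, not that it will happen. This is a cheap improvement rather than a fatal flaw.

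**What to change.** Replace the screening sentence in section 2.6.1 with a covariate set that is fixed before any post-test (T2) data are seen and used for both cohorts:

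- the three strategy factors;
- the baseline value of the outcome, where it is collected;
- cohort, in the pooled analysis;
- at most one named school-level covariate, for example school size.

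Include student age and sex only where the outcome does not already account for them. BMI percentile uses growth-chart norms, and the fitness estimate already has age and sex in its equation. Keep the bivariate summaries as description, and put any other predictor in a labelled sensitivity analysis.

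This leaves 4 school-level df per cohort, or 3 with the one school-level covariate (half-width 1.96, or a median of 2.40, SDs of school means). Pooled, it leaves 11 or 10 (1.10 or 1.14). The cost is a change of wording, with no new data. The small downside is that a strong but unforeseen predictor stays out of the main model.

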## Discussion

3

This study uses rigorous implementation science frameworks and methodologies to develop an implementation strategy for the HSRC initiative. In particular, the use of the MOST framework to develop, and a factorial design to test, the implementation strategies allow for the individual evaluation of three different discrete implementation strategies – additional resources, school-to-school mentoring, and enhanced engagement – and the understanding of potential interactions between these discrete strategies (26, 38). This is a substantial advancement within the field of implementation science, as most implementation strategy developers currently develop and test implementation strategies as packages (e.g., multiple strategies compared to control condition) (26, 38). Testing of implementation strategies as a package prevents understanding of how individual components within a package affect one another (e.g., antagonistic or synergistic interactions between components), which means that if the strategy needs to be adapted in the future (e.g., components removed), then another trial may be required, ultimately slowing the rate at which programs can be successfully delivered in practice. This study will provide effect estimates for each individual strategy and all combinations of strategies; thus, future researchers and practitioners will be able to use our outcomes to inform implementation of school-based interventions with seven different combinations of implementation strategies (i.e., three discrete strategies, three 2-way interactions, and one 3-way interaction), as opposed to the one effect estimate offered by a randomized controlled trial.

Implementation strategies that are used in this study were developed using school and community stakeholder input (e.g., extension agent) (29, 35). By using data from interviews and focus groups with local stakeholders and spending data from previous implementation efforts of HSRC (29, 35), we hope that we have developed strategies that are well-aligned with community needs and resources. Previous literature asserts that implementation strategies that are developed using stakeholder input are more impactful and equitable than implementation strategies that are developed without that type of input (65, 66). Given that the HSRC initiative is being implemented in a high cardiovascular disease risk area, we hope that obtaining and applying community stakeholder input in the development of the implementation strategies used in this study can improve the relevancy of these strategies to the local context. If so, this process may be replicated to improve the implementation of evidence-based interventions in other contexts.

We also evaluate implementation outcomes and effectiveness outcomes. By presenting a hypothesized logic model of the pathway between implementation strategies, implementation outcomes, and effectiveness outcomes, we can begin to understand how changes in short-term and long-term implementation outcomes affect program effect sizes for behavioral and health outcomes. Although current knowledge suggests that improved implementation of programs leads to improved health outcomes for participants, it is less clear which barriers to implementation are most important to address to improve implementation outcomes, which implementation outcomes have the biggest impact on improvements in effectiveness, and the strategies that can be used to address barriers. As previous literature demonstrates, there are at least 22 different barriers to the implementation of school-based programs (20, 21), over a dozen different implementation outcomes (67) and 75 different implementation strategies that can be used in the school setting (68). By proposing and evaluating how implementation strategies are related to barriers, implementation outcomes, and effectiveness outcomes, our work can begin to identify important pathways for improving the delivery and effectiveness of physical activity and healthy eating programs in the school setting.

Finally, the HSRC initiative bundles programs within the school setting to try to improve physical activity, healthy eating, and MetS risk among students. More specifically, all students at the school participate in an 8-week school-wide walking program (i.e., Walk Across Texas) (69, 70), and smaller groups of students at the school (e.g., physical education class, after-school club) participate in additional programming. This type of bundled approach is ideal for Extension agents, as once they start delivering programs at the school, it is often easier to implement additional programs within the school setting. Additionally, schools are an important setting to improve physical activity and diet quality among youth, as students spend an average of 6.5 h there each day for over 180 days each year (9), and school-based programs are an evidence-based approach for improving obesity outcomes (5–8). Still, given that bundled approaches have had mixed effectiveness in the clinical setting (13), it is unclear if this type of bundled approach has positive effects on students’ behavioral (i.e., physical activity and healthy eating) and health outcomes within the school setting. Thus, our study will evaluate changes in health outcomes over the course of one school year. Furthermore, as the HSRC initiative also requires that parents and/or school staff participate in a physical activity and healthy eating program – recommendations aligned with school health and ecological models (15–18)– we will evaluate physical activity and nutrition outcomes in these groups to determine if HSRC has any impact beyond students. These results can help to inform further modification to the way the HSRC initiative is designed and implemented within the school setting.

### Conclusion

3.1

Overall, this study aims to evaluate the individual and combined (synergistic or antagonistic) impact of three implementation strategies on the delivery of bundled physical activity and nutrition programs and evaluate the effectiveness of this approach on improving MetS among elementary school aged children. By using rigorous implementation science frameworks, developing three implementation strategies – additional resources, school-to-school mentoring, and enhanced engagement – and evaluating implementation and effectiveness outcomes, this study aims to determine which implementation strategies have the most impact on improving the delivery of a school-based initiative to deliver multiple research-based physical activity and nutrition programs. The results from this study can inform researchers and practitioners on the appropriate processes for developing and evaluating the delivery of bundled programs within a school setting. Furthermore, the implementation strategy or combination of strategies that have the biggest impact on outcomes can be scaled up to improve the delivery of the HSRC initiative within other schools across Texas and the United States.
